#### Assessment protocol

Primary and secondary physiological outcomes will be simultaneously recorded with participants sitting in their wheelchair, according to the following protocol: (i) resting phase of 5 min (after 2 min of habituation); (ii) mental challenge task (e.g. Stroop test) of 5 min; (iii) recovery phase of 5 min (resting and spontaneous breathing); (iv) breathing task of 5 min (paced breathing at 6 breath/min); 5-min recovery of 5 min (resting and spontaneous breathing). To control circadian influences, assessment will occur in the mornings (9 am-1 pm) and will be conducted in a quiet temperature-controlled room in the research laboratory. Participants will be asked to refrain from alcohol, caffeine and smoking at least 12 h before the assessment and to empty their bladder at the arrival to the laboratory.

### Secondary outcome measures- self-report (online) interview/assessment

#### Autonomic dysfunction Follgeowing spinal cord injury (ADFSCI)

This questionnaire is a measure of self-reported frequency and severity of symptoms during hypo- and hypertensive episodes [44]. It has been shown to correlate with blood pressure (BP) instability and to have acceptable test-retest reliability [44].

#### Spinal cord injury secondary conditions scale (SCI-SCS)

SCI-SCS assesses secondary physiological conditions that are associated with SCI using a 4-point ordinal 16-item scale ranging from 0 (not experienced/insignificant problem) to 3 (significant/chronic problem) [45]. Participants rate how these conditions have affected their activities and independence in the last 3-months. Examples of secondary conditions include pressure ulcers and bladder dysfunction. Higher scores indicate more significant impact [45].

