### Procedure

The RCT will involve the 120 adults being randomly allocated to either a HRV-F group or a no-treatment control group. Both groups will be similarly assessed over a period of 12-months, that is, at baseline, 10 weeks post-baseline (immediately after the HRV-F treatment for the intervention group), and at 6 and 12-month post-baseline. To test the feasibility of the RCT, the first 10 RCT participants with SCI who meet inclusion and exclusion criteria (5 in the HRV-F and 5 in the control arm) will be monitored for adherence to the HRV-F therapy and assessment, and for any barriers to the intervention and control group membership. The implementation study will involve conducting a mixed methods approach (qualitative and quantitative) to establish how best to translate HRV-F interventions into the community.

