### Randomization and blinding

RCT participants will be randomized to either the HRV-F group (*N* = 60) or to the no-treatment control group (N = 60) following a stratified randomization procedure. The randomisation allocation ratio is 1:1, while controlling for covariate level of injury (at and above T3 versus below T3). The randomization sequence will be computer generated via RAND function in Microsoft Excel by an independent person and then be uploaded into REDCap. Once the participant is recruited and completed the baseline assessment, then the assessor will inform the team members who are conducting the intervention. The researcher will then randomize a participant via pre-defined randomization sequence in REDCap (see Fig. 1). Team members responsible for recruitment, assessment and analysing the data will be blinded to group allocation. However, the researcher conducting the intervention as well as the participants will be aware of group allocation given it is not possible to blind them to the HRV-F versus control conditions.

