### Physiological assessment

See Table 1 for all primary and secondary outcome measures and endpoints (baseline versus 10 weeks, 6 and 12 months) for the RCT and implementation phase. The physiological assessment protocol includes:
(i)Activity #1: 5-min resting baseline (spontaneous breathing) after 2-min habituation;(ii)Activity #2: 5-min Stroop test;(iii)Activity #3: 5-min recovery (spontaneous breathing);(iv)Activity #4: 5-min breathing task (paced breathing at around 6 breath/minute);(v)Activity #5: 5-min recovery (spontaneous breathing).

**Table 1 Tab1:** Schedule of activities and measures for the RCT and implementation study. All psychometric instruments are scientifically validated and reliable

PROJECT STAGE *(number of participants)*			RCT (***N*** = 120) Pilot and main study phase)						Implementation phase (***N*** = 100)
**TIMELINE/PHASES***(D- day, W: week; M: month; Ph: phase)*			**-7D to 0D**	**0D**	**10 W**	**6 M**	**12 M**	**Fortnightly**	**Ph-1 to Ph-5**
**RECRUITMENT**	**ACTIVITIES**	**Mode of data collection**							
Screening	Eligibility checklist	In-person	**✓**						
	ISCoS cardiovascular function dataset	In-person	**✓**						
	ISCoS pulmonary function basic data set	In-person	**✓**						
Consent procedure	Informed consent procedure	In-person	**✓**						
**PARTICIPANT DESCRIPTORS**	**ASSESSMENTS**	**Mode of data collection**							
Socio-demographics	Socio-demographics details	In-person or online		**✓**					
Pre-injury details	Employment history and psychological status	In-person or online		**✓**					
Medical history	Self-report past/present health history	In-person or online		**✓**					
Injury characteristics	Level of lesion, AIS and FIM	Medical records		**✓**					
Pulmonary function	Pulmonary function test	In-person		**✓**					
**ALLOCATION**	**DESCRIPTION**	**Mode**							
Intervention group	HRV-F + Usual care	In-person and online							
Control group	Usual care	Online							
**PRIMARY OUTCOMES**	**OUTCOME MEASURE**	**Mode of data collection**							
Autonomic function	ECG/ HRV Time domain – Short term	In-person		**✓**	**✓**				
	ECG/ HRV Frequency domain – Short term	In-person		**✓**	**✓**				
Cerebral basal artery blood flow	Doppler assessment – Short term	In-person		**✓**	**✓**				
**SECONDARY OUTCOMES**	**OUTCOME MEASURE**	**Mode of data collection**							
Autonomic function	ECG/ HRV Time domain – Long term	In-person		**✓**		**✓**	**✓**		
	ECG/ HRV Frequency domain – Long term	In-person		**✓**		**✓**	**✓**		

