	ADFSCI questionnaire	In-person		**✓**	**✓**	**✓**	**✓**		
Cerebral basal artery blood flow	Doppler assessment – Long term	In-person		**✓**		**✓**	**✓**		
Neurophysiological function	Continuous BP	In-person		**✓**	**✓**	**✓**	**✓**		
	EEG	In-person		**✓**	**✓**	**✓**	**✓**		
	NIRS	In-person		**✓**	**✓**	**✓**	**✓**		
	EOG	In-person		**✓**	**✓**	**✓**	**✓**		
	Skin conductance, BVP, respiration and temp	In-person		**✓**	**✓**	**✓**	**✓**		
Secondary health conditions	SCI-SCS	In-person and online		**✓**	**✓**	**✓**	**✓**		
Cognitive function	NUCOG	In-person and online		**✓**	**✓**				
	Stroop test	In-person and online		**✓**	**✓**				
Psychological/mental health function	GADS	In-person and online		**✓**	**✓**	**✓**	**✓**		
	PHQ-9	In-person and online		**✓**	**✓**	**✓**	**✓**		
Psychosocial function	ISCoS pain questionnaire	In-person and online		**✓**	**✓**	**✓**	**✓**		
	FSS	In-person and online		**✓**	**✓**	**✓**	**✓**		
	PSQA	In-person and online		**✓**	**✓**	**✓**	**✓**		
	PCS	In-person and online		**✓**	**✓**	**✓**	**✓**		
Personal factors	*CD-RISC2 Short Form*	In-person and online		**✓**	**✓**	**✓**	**✓**		
Quality of life	*EQ-5D-5L*	In-person and online		**✓**	**✓**	**✓**	**✓**		
Participation and disability	*WHODAS domain – participation items*	In-person and online		**✓**	**✓**	**✓**	**✓**		
Consumer perception and satisfaction	Self-reported perception of change and satisfaction	In-person and online			**✓**				
Costs for Economic evaluation	Self-reported direct and indirect costs	Diaries (up to 12 m)						**✓**	
Adverse events	*Self-monitoring of Adverse events*	Diaries (up to 12 m)						**✓**	
Self-monitoring *of mood, breath rate, pain, fatigue and sleep quality*	*Numeric rating scale (0 to 10)*	Diaries (up to 12 m)						**✓**	
**EXPLORATORY OUTCOMES**	**OUTCOME MEASURE**	**Mode of data collection**							
Personal factors	*WHO ASSIST*	In-person and online		**✓**	**✓**	**✓**	**✓**		
	*COPE inventory – brief*	In-person and online		**✓**	**✓**	**✓**	**✓**		
	*ADAPSS – Short-form*	In-person and online		**✓**	**✓**	**✓**	**✓**		
	*MSES*	In-person and online		**✓**	**✓**	**✓**	**✓**		
Psychological/mental health function	PTSD Checklist 5	In-person and online		**✓**	**✓**	**✓**	**✓**		
Psychosocial function	SSQ6	In-person and online		**✓**	**✓**	**✓**	**✓**		
	Berlin Questionnaire	In-person and online		**✓**	**✓**	**✓**	**✓**		
Environmental factors	*Care, family and compensation status questionnaire*	In-person and online		**✓**	**✓**	**✓**	**✓**		

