#### Self-reported satisfaction with health services received and change in health

Two in-house Likert scales that assess the participant’s perceived satisfaction with received health services and their change in their health over the past 3 months.

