#### World Health Organisation alcohol, smoking, and substance involvement screening test (WHO ASSIST)

Question 2 of the WHO ASSIST requests information on the frequency of use of ten substances during the past 3 months, including substances such as tobacco, alcohol, cannabis, cocaine, amphetamine-type stimulants, inhalants, sedatives, hallucinogens, opioids, and ‘other’ drugs [64]. Responses are scored on a 5-point Likert scale, from ‘never’ to ‘daily or almost daily.’ Reliability of the WHO ASSIST has been demonstrated [65].

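### The study's own change-in-health item looks back 3 months but is given only at 10 weeks, so its reference point lies about 3 weeks before baseline; the 10-week SCI-SCS has the same overlap

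*Protocol article*

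**What the plan says.** The protocol article's section on self-reported satisfaction and change in health describes two Likert scales made for this study, on "perceived satisfaction with received health services and their change in their health over the past 3 months". Table 1 lists them as "Self-reported perception of change and satisfaction" with one tick, which in the extracted table stands under 10 weeks. There is no baseline tick and no later one.

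The SCI-SCS section states that instrument's recall: "Participants rate how these conditions have affected their activities and independence in the last 3-months". Table 1 places it under "Secondary health conditions" as a secondary outcome, with ticks at baseline, 10 weeks, 6 months and 12 months.

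Two further statements fix the timing. The Procedure section puts the first follow-up at "10 weeks post-baseline (immediately after the HRV-F treatment for the intervention group"). The section on randomisation and blinding puts allocation after the baseline visit: "Once the participant is recruited and completed the baseline assessment, then the assessor will inform the team members who are conducting the intervention". Only then is the participant randomised.

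No section shortens the recall at the 10-week visit or ties it to baseline. The exploratory WHO ASSIST, on "frequency of use of ten substances during the past 3 months", is also ticked at 10 weeks.

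**The concern.** A 3-month recall does not fit inside a 10-week interval. The other recall periods that the article states do fit: two weeks for the GAD-7 and PHQ-9, one month for the CD-RISC2 and four weeks for the short PCL-5. The 3-month instruments are the exceptions.

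For the change-in-health item, a participant who follows the wording compares health now with health some weeks before entering the trial. The answer then mixes change before randomisation with change after it. Because the item is scheduled only once, no second reading is available with a reference point after randomisation.

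For the SCI-SCS, the 10-week rating covers some time when nobody had been allocated, and it shares those weeks with the window already rated at baseline. At stake is the sensitivity of the short-term comparison on these secondary outcomes.

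**Working it through.** The plan gives no figure of its own on this point, so the check is window arithmetic on its stated recall and visit times.

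**Inputs**
- Recall: 3 months, taken as 89 to 92 days (91 as the central value), or 84 days if read as 12 weeks.
- First follow-up: 10 weeks = 70 days after baseline (Procedure).
- Randomisation after the baseline assessment, so no treatment before day 0 (Randomization and blinding).

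**Overlap before baseline = recall − 70; share = overlap / recall**
- 89 days: 19 days, 19/89 = 21%
- 91 days: 21 days, 21/91 = 23%
- 92 days: 22 days, 22/92 = 24%
- 84 days: 14 days, 14/84 = 17%

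**Change-in-health item.** Write H(t) for health on day t. With a 91-day recall the item asks for

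H(70) − H(−21) = [H(70) − H(0)] + [H(0) − H(−21)].

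The first bracket is change since baseline. The second is complete before allocation, so its expectation is the same in both arms and it cancels from the expected arm difference. The expected treatment effect is therefore intact. What changes is the spread: the second bracket contributes its own variance plus twice its covariance with the first. The documents give no standard deviations or correlations, so this noise cannot be sized.

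**SCI-SCS at 10 weeks.** This item rates a period, so the weight that respondents give to each part of it matters. That weighting is an assumption; the documents do not state it.
- Even weighting, effect constant from day 0: 70/91 = 77% of the effect shows (70/92 = 76% to 70/89 = 79%; 70/84 = 83% for 12 weeks).
- Even weighting, treatment starting 1 or 2 weeks after baseline with the visit fixed at day 70: 63/91 = 69% or 56/91 = 62%.
- Recent weeks weighted more, for example weights rising linearly from zero at the start of the window: the oldest 21 days carry (21/91)² = 5% of the weight, so about 95% shows.

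**Later SCI-SCS visits.** Counted from baseline, as in Procedure, the 6-month window opens at about 182.6 − 91.3 = day 91 and the 12-month window at about 365.3 − 91.3 = day 274. The Abstract counts these visits from the end of treatment; that reading moves the openings to about days 161 and 344. Either way both windows lie wholly after randomisation and after the 10-week course.

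**The case against.** The strongest reply is that little follows from the overlap. The primary outcomes are physiological recordings without recall. The SCI-SCS is repeated at 6 and 12 months with clean windows, and the planned repeated-measures mixed models can use those visits. No section names 10 weeks as its main time point, and choosing one can be left to an analysis plan that is not shown. The overlap is the same in both arms. All of this stands, and it is why the point is minor.

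A reader might also infer more than the documents support:
- *The arm difference on perceived change is pulled towards zero.* It is not. The item compares now with a reference point and does not average over a period. Any benefit at week 10 is fully contained in the current state.
- *Only about 38% of an effect would show.* That figure is 0.5 × 70/91 and assumes linear build-up over treatment. A recall of exactly 10 weeks, with no overlap, would still give 50%. Only the 70/91 factor belongs to the overlap.
- *Both in-house scales are affected.* The 3-month phrase may govern only change in health; the wording leaves this open for satisfaction.
- *The SCI-SCS is diluted by a known amount.* The 77% rests on even averaging, which nothing in the article establishes.

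What the reply does not meet is the change item: it has one scheduled reading, and that reading starts from the wrong date.

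**Conclusion.** The mismatch is real and follows from the article's own recall periods and visit times. It is minor. It is firmest for the change-in-health item, whose only reading starts before randomisation and so carries noise of unknown size without bias.

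For the 10-week SCI-SCS, some loss of sensitivity is the expected direction, but its size is conditional: about a quarter of a constant effect under even averaging with treatment from day 0, and much less if recent weeks dominate. The exploratory WHO ASSIST shares the overlap.

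The documents do not support the inference that the trial would report a real benefit as none, or that its main conclusions are at risk. An overlap common to both arms cannot produce a spurious benefit either. The reading of Table 1 rests on the extracted column positions.

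**What to change.** Reword the change-in-health item at the 10-week visit so that it asks about change *since your baseline assessment*. Do the same for the satisfaction item if the 3-month phrase is meant to cover it; if it is not, say so. These are the study's own scales, so only their wording changes.

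Keep the SCI-SCS wording. Interpret its 10-week result as supportive of the 6- and 12-month results; one line in the analysis plan would settle this. The 10-week WHO ASSIST can be read with the same caution.

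The cost is a small wording change and a slightly less prominent short-term SCI-SCS result. No visit, instrument or sample size changes.

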#### Cognitive assessment

The Neuropsychiatry Unit Cognitive Assessment Tool (NUCOG) [46, 47], a neurocognitive measure validated for SCI, will be used to assess cognitive functioning using age-adjusted normative scores from a scoring manual. The NUCOG domains include: attention, visuoconstructional ability, memory, executive, and language. Items needing hand function (e.g., object reproduction) will be modified as in prior studies where this has been demonstrated not to alter validity of NUCOG scores [47]. Where it is not possible to administer NUCOG assessments face-to-face (e.g., due to social distancing restrictions due to COVID-19), administration will occur by online methods [10].

#### Generalised anxiety Disorder-7 (GAD-7)

GAD-7 is a seven-item psychometric tool that assesses severity of generalized anxiety and probable generalized anxiety disorder (GAD) [48]. Items request individuals to rate severity of anxiety symptoms experienced over the prior 2 weeks. High scores represent more severe generalized anxiety symptoms. GAD-7 has demonstrated reliability and validity [48].

#### Patient health Questionnaire-9 (PHQ-9)

PHQ-9 assesses nine Diagnostic and Statistical Manual of Mental Disorders (DSM) criteria for depressive disorder over the prior two-week period [49]. Items range between 0 ‘not at all’ to 3 ‘nearly every day’, with higher scores indicating more severe depressive mood. PHQ-9 has demonstrated reliability and validity [49].

#### International spinal cord injury basic pain dataset

This includes four numerical rating items ranging from 0 (no pain) to 10 (extreme or worst pain) for pain intensity and pain interference in day-to-day activities, mood and sleep [50]. Numerical pain rating scales have demonstrated acceptable test-retest reliability and validity [51].

#### Fatigue severity scale (FSS)

The FSS is a 9-item self-report scale that measures fatigue and its influence on lifestyle and function [52]. Items are scored on a 7-point Likert scale (1 = strongly disagree and 7 = strongly agree). Higher scores suggest more severe fatigue. The FSS has demonstrated validity [52].

#### The Pittsburgh sleep quality index (PSQI)

PSQI measures sleep quality across seven domains: subjective sleep quality, sleep latency, sleep duration, habitual sleep efficiency, sleep disturbances, use of sleep medication, and daytime dysfunction [53]. Scoring employs a 0–3 Likert scale, with high scores indicating poor sleep. The PSQI has demonstrated validity [53].

#### Pain catastrophizing scale (PCS)

The PCS is a cognitive bias self-report scale consisting of 13-items that measure degree of catastrophizing type thinking a person is using (e.g., “I can’t stop thinking about how much it hurts”). Items are scored 0–4, with a total score of 54. Higher scores suggest more significant cognitive bias/pain catastrophizing [54]. The PCS has been shown to be reliable and valid [54].

#### Connor-Davidson resilience scale (CD-RISC2)

CD-RISC2 is a 2-item brief version of the 25-item CD-RISC. It measures perceived resilience over the past month with higher scores reflecting greater resilience [55]. The two items are ‘able to adapt to change’ and ‘tend to bounce back after illness or hardship’. The CD-RISC2 has demonstrated internal consistency, test-retest reliability, convergent validity, and divergent validity, and correlates well with the full scale [55].

#### EUROQOL version 5D-5L (EQ-5D-5L)

EQ-5D-5L includes five dimensions about aspects of health, that is, mobility, self-care, usual activities, pain/discomfort, and anxiety/depressive mood [56]. Dimensions have five levels of response, from “no problems” to “extreme problems”. Participants are asked to indicate the most appropriate response-level for each of the five dimensions. The EQ-5D-5L has demonstrated validity [56].

#### World Health Organization disability assessment schedule-participation domain (WHODAS-2)

The WHODAS-2 is disability assessment instrument based on the International Classification of Functioning, Disability, and Health (ICF) [57]. It provides a global measure of disability and 7 domain-specific scores. Only the Participation domain is being assessed. The WHODAS-2 has demonstrated validity [57].

#### Self-reported satisfaction with health services received and change in health

Two in-house Likert scales that assess the participant’s perceived satisfaction with received health services and their change in their health over the past 3 months.

### Health-related cost, adverse events and monitoring of the mood, breath rate, pain, fatigue and sleep quality

These variables will be measured using a fortnightly participant’s diaries.

### Exploratory outcome measures- self-report (online) interview/assessment

#### Post-traumatic stress disorder checklist short-form (PCL-5-SF)

PCL-5-SF is a 4-item version of the 20-item PCL-5. This abbreviated version has demonstrated reliability for detecting symptoms of post-traumatic stress disorder (PTSD) [58]. Participants are asked to rate symptoms experienced over the past 4 weeks including avoidance, negative changes in cognition and mood, and changes in arousal and reactivity. This is done on a 5-point Likert scale from ‘not at all’ to ‘extremely often’. Higher scores suggest more severe traumatic stress [58].

#### Brief coping orientation to problems experienced (brief COPE)

Brief COPE is a 28-item self-report questionnaire assessing ways of coping with stressful life events [59]. Only questions 2, 3, 7, and 8 of the Brief COPE will be included to minimize assessment time. The four items assess ‘Active – Approach’ and ‘Avoidant – Denial’ coping styles [59].

#### Social support questionnaire short form (SSQ-6)

The SSQ-6 is a 6-item questionnaire assessing perceived social support, such as the number of people participants believe are available for social support, and how satisfied they are with the level of support they receive. Items are scored from ‘very dissatisfied’ to ‘very satisfied’ on a 6-point Likert-type scale. The SSQ6 has demonstrated validity [60].

#### Moorong self-efficacy scale (MSES)

MSES measures self-efficacy related to expectations of control about functional activities of daily living in individuals with SCI [61]. Participants are asked to rate perceptions of their belief about their ability to manage 16 tasks on a 7-point Likert scale with 1 being very uncertain and 7 being very certain. Higher scores suggest higher perceived self-efficacy to perform functional activities [61].

#### Appraisals of DisAbility: primary and secondary scale (ADAPSS) short-form

ADAPSS Short-Form measures SCI-specific appraisals using 6 items from the full ADAPSS scale. It has a 2-factor structure of “catastrophic negativity” and “determined resilience”. The ADAPSS Short-form has demonstrated validity [62].

